| **Background and Aim of the study:** | In this study, the effectiveness of home- based cupping massage shall be tested in comparison to relaxation training in chronic non-specific neck pain patients. Therefore neck pain intensity (VAS), pain at motion (PRTM), pain quality (SBL), specific disability (NDI), well-being (FEW16), stress perception (PSQ20) quality of life (SF-36), anxiety and depression (HADS) as well as locus of control (GKÜ) will be measured. Pressure pain sensitivity (PPT) will be determined at pre-specified muscles.  In a daily log, pain intensity, medication and concurrent therapies will be noted. Personal experiences, changes and the influence of the therapy on partnership issues will be investigated with a qualitative interview at the end of the study.  Safety will also be evaluated. |
| **Design:** | Randomised controlled monocentric interventional study with 2 parallel groups:   - Home-based cupping massage, introduction in workshop, afterwards 2xweekly application for 12 weeks - Progressive muscle relaxation, introduction in workshop, afterwards 2xweekly application for 12 weeks. After termination of the study patients in this group will be offered home-based cupping massage.   Outcome assessors are blinded. |
| **Study centre:** | Essen-Mitte Clinics, Department of Internal and Integrative Medicine |
| **Number of patients:** | 42 Patients per group, i.e. 84 Patients in 2 groups. Estimation of patients needed according to ethics protocol no. 09-3987. |
| **Duration of study:** | Per Patient 4 months, 6 months for the complete study |
| **Inclusion criteria:** | - Age between 18 and 75 years - chronic non-specific neck pain for at least 3 months with intensity > 45mm VAS - Partner for administration of cupping massage (family, friends) - Medical records for anamnesis |

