- Severe psychiatric disorder
- Severe comorbid disorder (e.g. diabetes mellitus with neuropathy, oncological disease)
- Long-time medication with corticosteroids >10mg Prednisolon-equivalent
- Opiate medication
- Recently started (within the past 6 weeks) or recently modified medication with influences on musculoskeletal pain, such as muscle relaxants, psychopharmacological
- Pregnancy
- Current participation in other clinical studies
  1. Examination
     1. Screening

Patients will be screened telephonically for inclusion and exclusion criteria. If eligible they will be invited for physical examination into the clinic.

- - 1. First round of examination

At T0 a physical examination, an orienting neurological anamnesis will be conducted by the study physician. All patients are asked to provide medical records. At T0 they are informed about the study in detail and they have the possibility to ask the study physician any question. Before they are included they have to provide written informed consent. The data of those patients, that do not meet the criteria, are also documented.

- - 1. Second round of examination

After the first examination all patients will be handed out a daily log, which was checked at the second examination. Only patients who regularly filled in the daily log (>80% of days) and whose pain on average was >45mm VAS, were randomized for the study.

- 1. Randomization

After the measurement at T1 all patients will be randomized into one of the two groups using a non-stratified block randomization with random varying block lengths. The statistician will draw random numbers using the random number generator ranuni“ from the SAS®-Software (release 9.2, SAS Inc., Cary NC, USA) and prepare sealed numbered opaques sorted in ascending order. As soon a patient is included into the study the opaque with the lowest number will be opened and the patient assigned to the stated group.

1. Intervention

All intervention will be performed at the patients’ home. Patients receive extensive training, written material as well as consumables (cupping glass, oil, CD for relaxation). For questions patients could contact the coordinator or physician at any time during the study.

- 1. Cupping massage

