Pressure pain thresholds will be determined using a Algometer from Somedic, as it was used in prior studies (protocol numbers 09-3895, 09-3896, 09-3987). Pressure will be increased in ramps of 40kPa/s until the patient reports pain additionally to pressure. The pressure measured at this moment will be documented and 3 measures will be averaged. The PPT will be measured at the site of maximal pain and bilaterally on defined muscles (levator scapu­lae muscle, semispinalis capitis muscle, trapezius muscle). The PPT at the right hand (Thenar) will serve for demonstration and estimation of reliability (Johnston, Jimmieson, Jull, & Souvlis, 2008).

After the intervention patients’ experiences with application, compliance and observed changes will be retrieved in interviews. Safety will also be measured.

The influence of application on partnership and the susceptibility to infection will be part of the interviews. They might provide information for further studies.

- 1. Measurement time points

The parameters are measured before intervention (T1) and post intervention (T2). No long term catamnesis will be included as patients in the relaxation group will also receive cupping at the end of the study.

The daily log will be used during the whole study. The seminstandardized interview will only be conducted at post-intervention (T2).

1. Outcomes
   1. Primary outcome

Change in pain intensity from T1 to T2

- 1. Secondary outcome
- Change in pain intensity, medication and concurrent therapies according to the daily log
- Pain at motion (PRTM)
- Neck pain specific disability (NDI)
- Pain quality (SBL)
- Well-being (FEW16)
- Anxiety and depression (HADS)
- Stress perception (PSQ20)
- Quality of life (SF-36)
- Locus of control beliefs (GKÜ)
- Pressure pain sensitivity (PPT)
  1. Exploratory outcomes

Experiences in application, compliance and observed changes during the study will be measured descriptively. Safety will be measured the same way.

The influence of cupping massage on partnership will be measured using semi-standardised interviews. The analysis will be conducted using the qualitative content analysis approach after Mayring (Mayring, 2008).

1. Statistics
   1. Estimation of required sample size

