A literature search revealed no interventional study on which the estimation could be based on. Therefore data of a non-reported trial (protocol no. 09-3987) were used. Analysis revealed a difference of -14.3mm on the VAS the effect size was d=0.66. This effect size was used for estimation, although the settings of the planned study were different from the prior study (application at home instead of in the clinic, longer treatment intervals, empathic partner instead of physician), which made it impossible to determine the effect to be expected.

Based on the effect size of 0.66, an α of 5% and a power of 80%, a two-sided t-test would require 38 patients per group, i.e. 76 per study. To compensate for 10% drop outs, 84 patients were to be included in the study.

- 1. Statistical analysis

All analyses are based on the intention to treat population, i.e. all randomized patients. Missing values are to be imputed using multiple Imputation technic (MCMC-Method). Altogether 50 complete data sets are generated that way (Procedure PROC MI der SAS/STAT®-Software), analysed and the differences will be averaged (Procedure PROC MIANALYZE).

The primary outcome will be analyses using analysis of covariance model, with group as binary covariate, baseline and expectation as linear covariates. An adjusted group difference will be estimated (incl. 95% confidence intervals) and the superiority of cupping will be tested using a two-sided t-test.

No interims analyses are planned. No adjustment of results is necessary.

For the secondary outcomes equal models will be used for analyses. Group differences and significance will only be interpreted descriptively.

1. Risk Benefit Analysis
   1. Cupping massage

Cupping massage is considered very safe and used routinely in the department for Complementary and Integrative Medicine. Patients were instructed in cupping massage for years now, and the feedback was positive. If used after correct anamnesis and in the absence of contraindications no risks have been reported. Formation of haematoma is transitory.

- 1. Relaxation

Relaxation exercises are often used in stress-associated diseases. The effects are mostly unspecific, no side effects are known.

- 1. Measurements

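### The primary ANCOVA leaves out the daily-log pain mean that every randomised patient has before randomisation, and the protocol does not say whether log pain enters the imputation

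*Protocol*

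**What the plan says.** **Primary model.** The synopsis (Statistics row) and the section Statistical analysis give the same covariate list for the change in VAS from T1 to T2: group, baseline and expectation. No log variable is named.

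**The log before randomisation.** Under Second round of examination, the log handed out after T0 is checked at T1. Randomisation is limited to patients who filled it in on more than 80% of days and "whose pain on average was >45mm VAS, were randomized for the study".

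**The log afterwards.** It records daily VAS pain, medication and concurrent therapies (Measurement instruments). Under Measurement time points, "The daily log will be used during the whole study". Its only stated analysis role is as a secondary outcome. The questionnaire VAS is taken only at T1 and T2.

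**Missing data.** "Missing values are to be imputed using multiple Imputation technic (MCMC-Method"), with 50 completed data sets and the SAS procedures named. The variables in the imputation model are not listed.

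**Sample size.** The input comes from an earlier unpublished trial: "Analysis revealed a difference of -14.3mm on the VAS the effect size was d=0.66". With that value the plan concludes that "a two-sided t-test would require 38 patients per group, i.e. 76 per study", and it raises the total to 84 as an allowance for 10% loss.

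**The concern.** A single VAS reading is a noisy measure of a patient's usual pain. A mean over many days is less noisy, and the trial holds that mean for every randomised patient because eligibility requires it. A model that fixes its covariates without it gives up precision already paid for.

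The second issue is the imputation. There is one post-baseline VAS. When T2 is missing and the imputation model holds only the analysis model's own covariates, those patients add no information on the group difference. Fifty data sets then return the complete-case result with a little simulation noise. Log pain recorded after randomisation is probably the best available predictor of a missing T2 VAS. Whether it is used decides whether the imputation does anything for drop-out that follows the course of pain.

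**Working it through.** **1. The plan's own figure.** Inputs from Estimation of required sample size: d = 0.66, two-sided α 5%, power 80%. The noncentral t calculation gives 37.02, so 38 per group, with 81.0% power at 38. The stated 38 is reproduced. For drop-out, 76 × 1.1 = 83.6, so 84; 76/0.9 = 84.4, so 85. The planned 84 covers 1 − 76/84 = 9.5% drop-out, which is close enough. The implied SD is 14.3/0.66 = 21.7 mm. The calculation takes no credit for covariates, so nothing in it depends on the log.

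**2. Gain from the baseline log mean.** The protocol gives neither correlations nor the number of days between T0 and T1, so these are assumptions: r = correlation of T1 and T2 VAS, ρ = reliability of a single reading, 7 log days with independent daily error, and 21.7 mm taken as the SD of the T2 VAS. T1 VAS and the log mean together then act as the mean of 8 readings:

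- R² with T1 VAS only = r²
- R² with both = r² / (ρ + (1 − ρ)/8)
- variance ratio = (1 − R² with both) / (1 − r²)

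| r | ρ | R², T1 only | R², both | Variance ratio | Power at 38 per group |
|---|---|---|---|---|---|
| 0.3 | 0.8 | 0.090 | 0.109 | 0.979 | 84.5% to 85.3% |
| 0.5 | 0.7 | 0.250 | 0.339 | 0.881 | 90.6% to 93.7% |
| 0.6 | 0.6 | 0.360 | 0.554 | 0.697 | 94.4% to 98.9% |

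Middle row: 0.25/(0.7 + 0.3/8) = 0.25/0.7375 = 0.339, and 0.661/0.75 = 0.881.

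The idealised range is thus a 2-30% cut, and both ends need trimming.

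- At the top, r/ρ = 0.6/0.6 = 1, meaning that true pain at T1 and T2 is perfectly correlated. That is not credible over 12 weeks of treatment. Selecting patients above 45 mm on the log also narrows its spread.
- At the bottom, chance imbalance in one more covariate costs about 1/71 = 1.4% with 76 patients: 0.979 × 1.014 = 0.993, a net cut of about 1%.

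A simulation with selection at 45 mm (38 per arm, 14 log days, ρ 0.5-0.7, true-pain correlation 0.6-0.8) gave variance ratios of 1.04 to 1.14 for T1 only against T1 plus log mean. That is a cut of 1 − 1/1.04 = 4% to 1 − 1/1.14 = 12%, and 1 to 3 points of power. The working range is roughly 1-12%, or about 0-3 points.

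**3. Imputation from the analysis covariates alone.** In simulation (84 patients, 50 imputations, 1,500 runs per setting), the imputed and complete-case ANCOVA estimates correlated 0.998-0.999. At 10% missing in one typical setting both had SD 0.2034.

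**4. Precision if the on-study log is added.** Let f be the share missing and q the assumed partial correlation of log pain with T2 VAS. Relative variance is 1 + f/(1 − f) × (1 − q²).

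| f | q | Relative variance | Effective n of 42 | Power at d = 0.66 |
|---|---|---|---|---|
| 10% | 0 | 1.111 | 37.8 | 80.8% |
| 10% | 0.5 | 1.083 | 38.8 | 81.8% |
| 10% | 0.8 | 1.040 | 40.4 | 83.4% |
| 20% | 0 | 1.250 | 33.6 | 76.0% |
| 20% | 0.5 | 1.188 | 35.4 | 78.1% |
| 20% | 0.8 | 1.090 | 38.5 | 81.6% |

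**5. Bias if drop-out follows logged pain and differs by arm (assumed).** With about 10% missing and drop-out rising with logged pain in the cupping arm only, imputation without the log gave −0.70 to −0.72 against a true −0.66. That is 0.04 to 0.06 × 21.7 = 0.9 to 1.3 mm too favourable to cupping. With the log it gave −0.66 to −0.67. A harsher case, response-driven drop-out of 5% against 20%, gave −16.1 mm without the log and −14.4 mm with it, for a true −14.3 mm. In both, the log was available for every drop-out.

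**The case against.** The strongest reply is that nothing here is an error. ANCOVA on baseline and expectation is valid and pre-specified. Leaving out a second, correlated baseline measure biases nothing, and the planned power does not rest on it. All of that stands: this is a missed efficiency.

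A reader might also infer that the log is left out of the imputation. The protocol does not support that. It names the method, the number of data sets and the software, and neither includes nor excludes any variable. A joint MCMC model holding the log would fit the text, and the list may be in a statistical analysis plan that is not shown. The statement that the imputation adds almost nothing is therefore conditional.

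Nor do the documents show that drop-out will depend on pain or differ by arm. They plan for 10% overall and give no split. The near-complete removal of bias is a best case. Table 1 ties the log to T0, T1 and T2, so a patient who misses T2 may never hand in the on-study pages. Under the data-protection section, withdrawal of consent deletes all of that patient's data.

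One could also read baseline as the log, since the synopsis labels T0 as baseline. But the outcome is the change from T1 and the questionnaire VAS is not taken at T0, so the T1 VAS is the natural reading. The covariate list itself is fixed in two places, so that part was not left to a later plan.

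**Conclusion.** The point holds as an improvement, not as a correction of a mistake. The closed covariate list omits a baseline measure that the eligibility rule guarantees. Including it would cut the variance of the group difference by roughly 1-12%, under assumed values of reliability and correlation and an assumed length of the baseline log. The validity of the planned test and the figure of 84 patients are unaffected.

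On imputation, the supported statement is narrower: the variables are not named, and naming them matters. With the analysis covariates alone, the method is complete-case ANCOVA in practice. With the on-study log, power rises by about 1 to 3 points at the planned 10% drop-out. The better reason to include it is protection against a bias of the order of 1 mm at about 10% missing, and more if drop-out is heavier and one-sided. That protection reaches only as far as the logs of drop-outs are in hand.

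**What to change.** - In the synopsis and in Statistical analysis, add each patient's mean log pain from T0 to T1 as a further linear covariate, and state that baseline means the T1 VAS. Cost: one degree of freedom, some wording, and entry of log data that must be checked for eligibility anyway.
- Name the imputation variables for T2 VAS: group, T1 VAS, baseline log mean, expectation, and on-study log pain in a few means, for example weeks 1-4, 5-8 and 9-12. The on-study means belong in the imputation model only. As post-randomisation measures they must not become covariates in the analysis model. Cost: wording and data entry.
- State that log pages are to be retrieved from patients who stop early and have not withdrawn consent, since the benefit depends on it. A pain rating at the existing 6-week call would help, but it is a change in data collection and is optional.

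The primary endpoint, the sample size and the interventions stay as they are.
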